### Statistical analysis

#### Sample size

Calculation of statistical power is based on the estimated effect of CGA based interventions on physical performance. According to a previous study focusing on patients with osteoarthritis, the clinically relevant change in the 30s-CST was set at 2.6 repetitions [58]. Based on results from prior studies focusing on patients with advanced cancer, a standard deviation (SD) of around 3 has been reported in the 30s-CST [59, 60]. To be able to detect a difference of 2.6 repetitions in the between-group difference in the 30s-CST at the 12-week assessment and to obtain a type I error rate of 5% and a power of 90%, a sample size of 29 patients per study arm will be needed. To account for an expected dropout rate of ~ 40%, we decided to increase this number to a group size of 50. Thus, the aim will be to include a total of 100 patients in the study.

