### Randomisation

Randomisation is performed electronically in REDcap randomisation module from permuted blocks and stratified for Eastern Cooperative Oncology Group (ECOG) performance status. Patients will be randomized 1:1 to an intervention group and a control group.

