### Endpoints and measurements

Baseline test prior to randomisation includes test of physical strength and capacity, questionnaire of quality of life and estimation of body composition. Study data are collected on the 2. and 14. postoperative day, and at the end of study 14 weeks after surgery (Fig. 2).

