### Primary endpoint

The primary endpoint of the GEPOC study is change in 30-s Chair Stand Test (30s-CST) from baseline to 14 weeks after surgery. The 30s-CST measures a combination of muscle strength and endurance and is highly sensitive in older patients [42]. A high test-score is regarded as a predictor for functional independence in older patients [43–45] as it measures the ability to rise from a chair. The 30s-CST has also been used and tested in cancer patients [46, 47].

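### The 90% power is calculated for a 30s-CST difference at a 12-week assessment that is not in the schedule, with what reads as a score SD; it is not shown for the declared endpoint, unadjusted change to week 14

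*Protocol article*

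**What the plan says.** The Primary endpoint section of the protocol article defines the outcome as "change in 30-s Chair Stand Test (30s-CST) from baseline to 14 weeks after surgery". Endpoints and measurements gives a baseline test before randomisation and then this schedule: "Study data are collected on the 2. and 14. postoperative day, and at the end of study 14 weeks after surgery". Secondary endpoints reports the physical tests at two and 14 weeks after surgery. None of these sections has a 12-week visit.

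The Sample size section states that "the clinically relevant change in the 30s-CST was set at 2.6 repetitions", that "a standard deviation (SD) of around 3 has been reported in the 30s-CST" in studies of advanced cancer, and that the trial is to detect "a difference of 2.6 repetitions in the between-group difference in the 30s-CST at the 12-week assessment". With a 5% type I error and 90% power, it concludes that "a sample size of 29 patients per study arm will be needed", raised to 50 per arm for about 40% dropout. It gives no SD of change and no correlation between baseline and follow-up.

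The Quantitative data section names independent t-tests, or Mann-Whitney and Wilcoxon tests, for continuous outcomes. It mentions no adjustment for baseline.

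**The concern.** There are two mismatches between the power statement and the declared endpoint.

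- **Time point.** The power statement refers to a visit that the schedule does not contain.
- **Quantity.** The endpoint is a change score, but the SD is described as that of the 30s-CST itself. The SD of a change equals the SD of the score only at one particular correlation between the two measurements, and the article gives no correlation.

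At stake is whether the 90% describes the analysis that will be reported. That matters most for reading a null result in a trial that expects to lose about 40% of its patients.

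**Working it through.** **Inputs.** From Sample size: difference 2.6 repetitions, SD 3, type I error 5%, power 90%, dropout about 40%. From Randomisation: 1:1 allocation. Assumed: a two-sided test (not stated, but it reproduces the stated number; a one-sided normal approximation gives 23 per arm).

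**Step 1: reproduce the stated figure.**

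- Normal approximation: n = 2 × 3² × (1.960 + 1.282)² / 2.6² = 27.98, so 28 per arm.
- Two-sample t-test (noncentral t): n = 28.97, so 29 per arm. Power is 90.0% at 29 and 89.0% at 28.
- Dropout: 29 / (1 − 0.4) = 48.3, so 49, which the plan rounds up to 50. Conversely, 50 × 0.6 = 30 completers per arm.

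The stated 29 is therefore a plain two-sample t-test with SD 3. Both steps of the calculation are correct.

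**Step 2: the time point.** The Exercise programme section has a two-week pause after surgery and then 12 weeks of training: 2 + 12 = 14 weeks. The end of the exercise block thus coincides with the end-of-study visit. No input to the calculation depends on whether the label is 12 or 14 weeks.

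**Step 3: the same calculation for an unadjusted change score.** Randomisation makes the expected group difference the same (2.6) for score and change, so only the SD differs. If 3 is the SD of the score at both times and r is the correlation between baseline and week 14, then

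SD of change = 3 × √(2(1 − r)).

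This equals 3 only at r = 0.5. The documents give no r, so the values below are assumptions (t-test, two-sided 5%).

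| r | SD of change | Power, 29 completers per arm | Completers per arm for 90% |
|---|---|---|---|
| 0.2 | 3.79 | 73% | 46 |
| 0.3 | 3.55 | 78% | 41 |
| 0.4 | 3.29 | 84% | 35 |
| 0.5 | 3.00 | 90% | 29 |
| 0.6 | 2.68 | 95% | 24 |
| 0.7 | 2.32 | 99% | 18 |

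With the 30 completers per arm expected from 50, power at r = 0.3, 0.4, 0.5, 0.6 and 0.7 is 80, 85, 91, 96 and 99%.

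**Step 4: the baseline-adjusted comparison.** Under ANCOVA the residual SD is 3 × √(1 − r²), which never exceeds 3. At r = 0.2, 0.3 and 0.4 it is 2.94, 2.86 and 2.75, and power with 29 per arm is 91, 92 and 94%. At r = 0 it is 3, and power is 90.0% even after one degree of freedom is spent on the covariate (55 instead of 56).

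If 3 is instead the SD of change, the bound still holds with equal score SDs: the squared ratio of ANCOVA SD to change-score SD is (1 − r²) / (2(1 − r)) = (1 + r)/2, which is at most 1.

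**The case against.** The case for leaving the plan alone has several parts, and most of it stands.

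- **The time point is only a label.** A reader might infer that the trial was powered for a different endpoint from the one declared. The documents do not support that: the exercise block ends at the 14-week visit, and relabelling changes no number. What remains is a wording conflict to reconcile.
- **The SD may already be that of change.** The paragraph speaks of a clinically relevant change and, awkwardly, of a difference in the between-group difference, so this reading is open. The sources behind the figure are not at hand. If 3 is the SD of change, the stated 90% is correct for the declared endpoint. But the text does not say so, and its literal wording points to the score.
- **The correlation could lie on either side of 0.5.** A reader might infer from the rows below 0.5 that the trial is underpowered. That does not follow, because above 0.5 the sample size is conservative. One may conjecture that surgery and complications between the measurements weaken the correlation, but nothing in the documents gives or bounds it.
- **The primary model may be specified elsewhere.** The Quantitative data section is a general paragraph, and a fuller protocol or SAP may name a baseline-adjusted model. That is possible, but the tests the article does name are unadjusted.

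A reader might also take this as a calculation error. It is not one, since the stated 29 and 50 both follow from the stated inputs.

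**Conclusion.** The point holds in limited form. The sample-size paragraph names a visit that is not in the schedule, most plausibly meaning the 14-week visit, and its SD is not tied to the declared change endpoint.

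The 90% carries over to an unadjusted comparison of change only if 3 is already the SD of change or, with 3 as the score SD, if r is at least 0.5. Over assumed r from 0.2 to 0.7, power with 29 completers per arm runs from 73% to 99%. So 90% is neither shown nor refuted for that analysis, and underpowering is not demonstrated.

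The range rests on a two-sided 5% test, equal score SDs at both times, a true difference of 2.6, and correlations that are assumptions. A baseline-adjusted analysis removes the dependence on r, because about 90% becomes its lower bound.

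**What to change.** 1. In Sample size, replace the reference to a 12-week assessment with 14 weeks after surgery, to match Primary endpoint and the schedule.
2. Make the primary comparison an ANCOVA of the week-14 30s-CST (or of the change, which gives the same treatment estimate) adjusted for baseline 30s-CST. State the sample size on that basis: score SD 3, difference 2.6, two-sided 5%, at least about 90% power with 29 completers per arm whatever the correlation.
3. If the unadjusted change score is kept, state that 90% assumes an SD of change of 3 (equivalently r = 0.5 if 3 is the score SD) and show power on both sides of that value, for example 78% at r = 0.3 and 99% at r = 0.7. Do not present 90% as a ceiling.

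The cost is rewording the sample-size paragraph and adding one sentence on the primary analysis. Baseline 30s-CST is already measured before randomisation, so no data collection is added and the target of 100 patients is unchanged.

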#### Quantitative data

Results from physical tests, body composition measures, questionnaires and serum biomarkers will be reported as means and standard deviations (SD) or as median and IQR, as appropriate. Change over time in ordinal categorical values will be evaluated by a trend test using logistic regression. In-group and between- group differences in continuous-level data, will be performed using independent T-tests or the nonparametric Mann-Whitney U and Wilcoxon tests, depending on their distribution. Survival analyses will be conducted using Kaplan-Meier method, competing risk analyses and Cox regression analyses. Using the Kaplan-Meier method the cancer-specific mortality and overall survival (OS) will be assessed for the intervention group and the control group, and comparison in survival between groups will be assessed using the log-rank test.

Statistical analyzes will be performed by a statistician in collaboration with the primary investigator ([name]) using R Version 1.0.153.

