### Secondary endpoints

**Muscle strength and functional capacity**: changes in hand grip strength, 6 m and 10 m habitual gait speed, 5-times-sit-to-stand and 6-min-walk-test. The 5-times-sit-to-stand is performed separately in accordance with latest guidelines for sarcopenia [48]**.** Changes in the physical tests will be reported from baseline at two and 14 weeks after surgery and changes from 2 weeks after surgery at 14 weeks after surgery. Additional information regarding the tests are described in Supplement 3. Cumulated Ambulation Score (CAS) [49] will be measured in the postoperative period, as a measurement of day-to-day basic mobility. For acute abdominal surgery a poor CAS is associated with pulmonary complications and low activity in the first postoperative week [50] and CAS has been shown to be predictive for discharge to a higher level of dependence [49]. CAS will be compared between groups and investigated as a predictor for poor postoperative outcome independent of patient allocation to control or intervention group. All physical tests will be performed in the same sequence by a physiotherapist blinded to patients’ allocation to control or intervention group.**Patient reported outcome measures:** Patient’s perspective of recovery in the perioperative period will be assessed with Quality of Recovery-15 (QoR-15). QoR-15 is a patient reported outcome questionnaire that quantifies recovery from surgery and anaesthesia [51, 52].Health related Quality of Life (HRQoL) will be assessed with European Organization for Research and Treatment of Cancer Quality of Life Questionnaire Core 30 (EORTC QLQ-C30) conjoined with the module for older patients with cancer (QLQ-ELD14). The questionnaires incorporate functional scales, symptom scales and a global health and quality-of-life scale [53, 54].**Postoperative complications (30 + 90 days):** The occurrence of postoperative complication within 30 + 90 days after surgical resection of CRC will be graded from 0 to 5 based on the classification system validated by Clavien and Dindo [55]. Further details are described in Supplement 4.**Body composition and sarcopenia:** Whole-body dual-energy X-ray absorptiometry (DXA) scan (GE lunar iDXA, GE Healthcare Technologies, Madison, Wisconsin, U.S.) and bioelectrical impedance (BI) assessment (Body Composition Monitor, Fresenius Medical Care, Bad Homburg v.d.H., Germany) will be used to measure body composition. Sarcopenia will be reported according to the revised guidelines from the European Working Group on Sarcopenia in Older People [48].**Length of stay and readmission rate:** The postoperative length of stay defined from the day of surgical resection of CRC to the day of discharge from the surgical ward will be calculated. Readmission rate is defined as any unplanned hospitalisation within 30 and 90 days of discharge is registered.**Initiation and completion of adjuvant chemotherapy:** Patients will be treated with adjuvant chemotherapy according to national guidelines if indication for chemotherapy is found [56]. Type of chemotherapy, dose, number of series and adverse events are registered.**Survival and mortality:** Cancer- and treatment-related mortality or other cause of mortality will be registered throughout the study and a during a follow-up period of 5 years.**Serum biomarkers:** Blood samples will be taken 1–3 days before surgery, at the first and second postoperative day and at the end of study. Serum biomarkers will be analysed as part of cooperative research project REBECCA (“Biomarkers for patients with colorectal cancer - providing new information on diagnosis, treatment effect, side-effects and prognosis” (translated from Danish)). The REBECCA study is approved by the Regional Ethics Committee (H-2-2013-078) and the Danish Data Protection Agency (jr. nr. 2007-58-0015; HEH-2014-044; I-suite nr. 02771 and PACTIUS P-2019-614).

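### The plan names the independent-samples t-test for within-arm change, which is paired data; the parametric within-arm standard errors would be too large

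*Protocol article*

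**What the plan says.** The Quantitative data section puts both kinds of comparison in one sentence: "In-group and between- group differences in continuous-level data, will be performed using independent T-tests". It goes on: "or the nonparametric Mann-Whitney U and Wilcoxon tests, depending on their distribution". No paired t-test is named, and no test is assigned to a particular comparison.

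The Secondary endpoints section shows what the in-group differences are: "Changes in the physical tests will be reported from baseline at two and 14 weeks after surgery". It adds the change from 2 to 14 weeks. Each of these compares two measurements on the same patient.

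The primary endpoint is "change in 30-s Chair Stand Test (30s-CST) from baseline to 14 weeks after surgery", which is one change score per patient. The sample size is set for a comparison between arms: "To be able to detect a difference of 2.6 repetitions in the between-group difference in the 30s-CST".

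**The concern.** The independent-samples t-test assumes that the two sets of values come from different people. For baseline against follow-up in one arm they come from the same people, and physical-performance scores in the same person are normally positively correlated. The variance of a paired difference is then smaller than the sum of the two variances, and the independent formula leaves out the covariance term that accounts for this.

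Followed as written, the rule makes each parametric within-arm confidence interval too wide and each p-value too large. The sentence covers continuous data in general, so it reaches any physical test, body composition measure, questionnaire score or biomarker that is analysed parametrically within an arm. The article names the test and names it wrongly, so this is not a detail left to a later document.

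**Working it through.** **Inputs from the article (Sample size section).** Between-group difference 2.6 repetitions; SD about 3 ("a standard deviation (SD) of around 3 has been reported in the 30s-CST"); "type I error rate of 5% and a power of 90"%; 29 per arm; about 40% dropout; 50 per arm enrolled.

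**Assumptions.** The within-patient correlation r is not given, so a range is shown. The SD of 3 is taken as the SD of a score at each visit; the article does not say whether it refers to a score or to a change. A within-arm change of 1.5 repetitions, used for one power comparison, is also assumed.

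**Step 1: reproduce the plan's own figure.** Two-sided normal approximation: n = 2 × (1.960 + 1.282)² × 3² / 2.6² = 27.98, so 28 per arm. The exact two-sample t calculation gives 28.97, so 29, as stated. Allowing for dropout, 29 / 0.6 = 48.3, so 49; the plan uses 50. Expected completers are 50 × 0.6 = 30 per arm.

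**Step 2: standard error of a within-arm change, n = 30.**
- Independent formula: 3 × √(2/30) = 0.775, whatever r is.
- Paired formula: 3 × √(2(1 − r)/30).
- Ratio: 1/√(1 − r), which depends on neither the SD nor n.

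**Step 3: operating characteristics.** 20,000 simulated trials per setting, 30 normally distributed pairs, nominal 5% two-sided.

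| Assumed r | Independent SE | Paired SE | Ratio | Type I error, independent test | Power for 1.5: independent / paired | Power for 2.6: independent / paired |
|---|---|---|---|---|---|---|
| 0.3 | 0.775 | 0.648 | 1.20 | 2.0% | 47% / 60% | 94% / 97% |
| 0.5 | 0.775 | 0.548 | 1.41 | 0.7% | 48% / 75% | 97% / nearly 100% |
| 0.7 | 0.775 | 0.424 | 1.83 | 0.1% | 47% / 93% | 99% / 100% |

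The paired test stays at about 5% throughout.

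**Step 4: between-arm comparison.** An independent t-test on one change score per patient, 30 per arm, has a simulated type I error of 5.0%, 4.9% and 4.9% at r = 0.3, 0.5 and 0.7. That use of the test is valid.

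**The case against.** The strongest reply is that the sentence is compressed, not mistaken. It names Wilcoxon beside Mann-Whitney U. The rank-sum form of Wilcoxon is equivalent to Mann-Whitney U, so listing both most naturally means that Wilcoxon is the paired signed-rank test. The authors probably know that within-arm data are paired, and a skewed variable would be handled correctly. This stands, and it limits the fault to the parametric branch. It does not remove the fault: on that reading the plan respects pairing when data look non-normal and ignores it when they look normal.

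It can also be said that within-arm tests in a randomised trial are descriptive, that a standard error that is too large creates no false positives, and that the loss of power depends on the change chosen. All of this stands. At 2.6 repetitions, the only relevant change that the article gives, the independent test still has 94% power or more. The large loss appears only for a smaller change such as the assumed 1.5.

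A reader might go further and infer that ordinal outcomes are to be analysed as if repeated values came from different patients, because the section says: "Change over time in ordinal categorical values will be evaluated by a trend test using logistic regression". The article does not support this. It does not say whether within-patient correlation is modelled, and an article commonly leaves that to the full protocol or analysis plan. Nor does the sentence show that the comparison between arms is neglected: it is limited to change over time, and the Secondary endpoints section separately says that the ambulation score will be compared between the groups.

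**Conclusion.** The rule is wrong as written, and the point is minor. Under any positive within-patient correlation, the parametric within-arm standard errors, intervals and p-values would be wrong. At 30 completers per arm the standard error is 1.2 to 1.8 times too large for correlations of 0.3 to 0.7, and the type I error falls to between 2.0% and 0.1%. These figures rest on the assumed correlations; the direction does not, provided that the correlation is positive.

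A reader might infer that the primary result or the sample size is compromised. Neither is. The primary endpoint gives one change score per patient, the independent t-test keeps its level for comparing those scores between arms, and the 29 per arm is calculated for a between-arm difference. Nor does the fault reach every within-arm result, since variables sent to the nonparametric branch are probably analysed as paired.

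**What to change.** Replace the sentence with one that assigns each test to its comparison, for example:

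*Within-group changes: paired t-test or Wilcoxon signed-rank test (descriptive). Between-group differences in change: independent t-test or Mann-Whitney U test, or preferably a model adjusted for the baseline value.*

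The baseline-adjusted model is a preference and is not needed to cure the pairing fault; the baseline values that it uses are already collected. The change costs one or two sentences, needs no new data and leaves the sample size as it is. The Trial status section reports 36 of the planned 100 patients included in January 2021, so at that point the wording could still be corrected before analysis.

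### The stated between-arm test for the primary change in 30s-CST uses neither baseline nor ECOG stratum as a covariate and lets the distribution choose between a t-test and a rank test, costing precision and leaving the primary effect measure unfixed

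*Protocol article*

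**What the plan says.** The primary endpoint (Primary endpoint section) is "change in 30-s Chair Stand Test (30s-CST) from baseline to 14 weeks after surgery". The Endpoints and measurements section places the baseline measurement before allocation: "Baseline test prior to randomisation includes test of physical strength and capacity". Under Randomisation, allocation is 1:1, drawn "from permuted blocks and stratified for Eastern Cooperative Oncology Group (ECOG) performance status".

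The Quantitative data section opens by listing the physical tests among the results it covers, so the 30s-CST falls under it. Its one sentence on continuous outcomes, covering within-arm and between-arm comparisons, reads "group differences in continuous-level data, will be performed using independent T-tests or the nonparametric Mann-Whitney U and Wilcoxon tests, depending on their distribution". No separate model is named for the primary endpoint. No covariate is named, and no criterion for judging the distribution is given. Regression appears in that section only for ordinal trends and survival.

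The Sample size section states its target as a difference in repetitions: "To be able to detect a difference of 2.6 repetitions in the between-group difference in the 30s-CST at the 12-week assessment". Of the variability it says only that "a standard deviation (SD) of around 3 has been reported in the 30s-CST". It does not say whether this is the SD of the score at one visit or of the change.

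**The concern.** Two things are fixed badly.

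First, precision. The baseline 30s-CST is measured before randomisation, and ECOG is important enough to stratify on, yet the stated test uses neither as a covariate. Subtracting baseline amounts to assuming a slope of 1 of follow-up on baseline. When the true slope is below 1, the change score carries avoidable variance, and part of any chance baseline difference between arms passes into the estimate. About 40% dropout is expected, which leaves about 30 completers per arm, so both effects matter at this size.

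Second, the effect measure. A t-test addresses a difference in means. A Mann-Whitney test addresses rank ordering. The trial is sized on a mean difference of 2.6 repetitions. If the distribution leads to the rank test, the primary result no longer estimates that quantity, and the reader cannot know in advance which will be reported.

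**Working it through.** **Inputs from the protocol article.** Difference 2.6 repetitions, SD about 3, type I error 5%, power 90%, 29 per arm before dropout, 50 per arm after about 40% dropout (Sample size); 1:1 allocation (Randomisation).

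**Assumptions.** The test is two-sided, which the article does not state; a one-sided normal approximation would give 23 per arm. The baseline-to-week-14 correlation r is not given, so a range of 0.3 to 0.8 is shown. The SD is taken as equal at the two visits.

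**Step 1: the plan's own figure.** A two-sample t-test with standardised difference 2.6/3 = 0.867, two-sided 5% and 90% power needs 28.97, so 29 per arm (28 by normal approximation). The stated figure reproduces and is that of an unadjusted t-test. 30/(1 − 0.4) = 50 per arm.

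**Step 2: variance.** With score SD s at both visits:
- SD of change = s·√(2(1 − r))
- residual SD under ANCOVA = s·√(1 − r²)
- ratio of variances = (1 − r²)/(2(1 − r)) = (1 + r)/2

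ANCOVA variance is therefore lower by 35% at r=0.3, 25% at r=0.5, 15% at r=0.7 and 10% at r=0.8.

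**Step 3: power at 29 per arm, if 3 is the SD of the score.**

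| r | SD change | SD ANCOVA | Power, change t-test | Power, ANCOVA |
|---|---|---|---|---|
| 0.3 | 3.55 | 2.86 | 78% | 92% |
| 0.5 | 3.00 | 2.60 | 90% | 96% |
| 0.7 | 2.32 | 2.14 | 99% | above 99% |

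**Step 4: power at 29 per arm, if 3 is the SD of change.** The planned test has its stated 90% whatever r is. The ANCOVA residual SD is 3·√((1 + r)/2).

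| r | SD ANCOVA | Power, change t-test | Power, ANCOVA |
|---|---|---|---|
| 0.3 | 2.42 | 90% | 98% |
| 0.5 | 2.60 | 90% | 96% |
| 0.7 | 2.77 | 90% | 94% |
| 0.8 | 2.85 | 90% | 93% |

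The ANCOVA powers put the smaller SD into the two-sample t formula. Estimating the baseline slope costs less than half a percentage point (at r=0.3 in Step 3, 29 replaced by 28.5 per arm gives 92.1% instead of 92.5%).

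**Step 5: chance imbalance.** Given a baseline difference d between arms, the expected change-score difference is the true effect minus (1 − r)·d. At r=0.5 and d = 1 repetition that is a shift of 0.5 repetitions, against a target of 2.6. ANCOVA removes it. Averaged over randomisations, d is zero.

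**Step 6: choosing the test by distribution.** In 10,000 simulated null trials with 30 per arm, a fixed Shapiro-Wilk rule gave a type I error of 5.1% for normal and 4.8% for skewed data. Taking the smaller of the two p-values gave 5.8% and 6.4%.

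**Not computable.** The gain from the ECOG term: neither its association with 30s-CST nor the number of strata is stated.

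**The case against.** The strongest reply is that the planned test is valid. Under 1:1 randomisation an unadjusted comparison of change is unbiased and keeps its type I error; leaving out the stratum tends, if anything, to be conservative. That stands. The loss is one of efficiency and of sensitivity to the imbalance in a particular sample.

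A reader might infer that the baseline 30s-CST is ignored. It is not: the change score subtracts it. The criticism is only that it is not a covariate.

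A reader might take 78% as the trial's real power. The article does not support that. The figure needs both the score reading of the SD and r=0.3. On the other reading the planned test has the 90% it claims, and at r=0.7 on the score reading both analyses have about 99%. Every stated gain depends on an r that the article does not give.

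A reader might also infer an inflated type I error from the choice of test. Under a fixed rule the simulation shows none. Inflation appears only if the smaller p-value is taken, which the article does not propose. What stands is that the effect measure is left open.

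It can also be said that covariates and the rule for judging distributions commonly sit in an analysis plan, which is not shown, and that this is one generic sentence in a condensed article. That would answer a complaint about silence. Here the article names the tests and makes the choice depend on the distribution, so it fixes a method, and that method can be improved.

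**Conclusion.** The point holds as a moderate, assumption-dependent loss of efficiency together with an unfixed primary effect measure. It does not show bias or an invalid test.

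The variance ratio (1 + r)/2 rests on equal variances at the two visits and favours ANCOVA for any r below 1, apart from a degree of freedom or two. The gain in power at 29 per arm runs from about 14 percentage points (score SD 3, r=0.3) to under 1 point (score SD 3, r=0.7). If 3 is the SD of change, it is between about 3 and 8 points. Confidence is high on what the article states and on the direction of the gain, but lower on its size, because neither r nor the meaning of the SD is given.

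The case for fixing one effect measure needs none of these assumptions: the sample size is built on a mean difference, and one of the two candidate tests does not estimate it.

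The point does not extend to the survival analyses. Cox regression is planned without a list of covariates, so nothing shows that ECOG is left out there.

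**What to change.** In the Quantitative data section, name one primary analysis, for example:

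> *Primary analysis: ANCOVA of 14-week 30s-CST on arm, baseline 30s-CST and ECOG stratum, reporting the adjusted mean difference with 95% CI. The method is not changed according to the observed distribution; a rank-based test is a sensitivity analysis.*

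Use the same model for the other continuous endpoints that have a baseline value.

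The cost is wording only. Baseline 30s-CST and ECOG status are already collected before allocation, and no extra patients or visits are needed. The sample size can stay as it is, since the adjusted analysis has at least the power of the planned one apart from a degree of freedom or two. The article reports recruitment still under way in January 2021 (Trial status); the change should be dated and made before any outcome is examined by arm.
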